**Intended/Potential Use of the Study Findings**

A recent study comparing the cost-effectiveness of HIV prevention interventions found that the two most important factors that determined cost-effectiveness were the HIV prevalence of the target population and the cost per person reached.30 In fact, one of the two most cost-effective interventions overall was showing videos in STI clinics (individual-level).30 These findings support our proposed online behavioral intervention using video vignettes in terms of cost-effectiveness and reaching high-risk MSM. If successful, this type of novel Internet-based intervention approach will be efficient, cost-effective, feasible to replicate, and especially useful in reaching men in rural areas or other hard-to-reach populations.

Specific Aims and Hypotheses

**Aim 1:** To test the feasibility of implementing an innovative national online randomized controlled, multi-branched, behavioral intervention for men who have reportedoral or anal sex with any male (new partner or not) in the past 60 days AND reported oral, anal or vaginal sex for the first time (new partner) with a male or female within the past 60 days.

**Aim 2:** a) To identify and recruit men who have sex with men met online or offline, and who, in the last 60 days, met a new sex partner; b) To enroll and randomly assign 3,000 MSM, representing diverse race/ethnicities and geography, into one control or four intervention conditions; c) To maximize retention 60-days post-intervention to complete the follow-up survey.

**Aim 3:** To evaluate the intervention conditions by comparing outcome risk measures (HIV disclosure, HIV testing, condom use, drug and/or alcohol use before sex, and depressive and/or anxiety symptomatology) at 2 time points for 5 study conditions.

**Aim 3 Primary Hypotheses:** Between baseline and 60-day follow-up there will be an increase in the following: a) HIV disclosure with new sex partners, b) HIV testing, and c) condom use in intervention branches 3, 4, and 5, compared to branches 1 and 2.

**Aim 3 Secondary Hypotheses:** Between baseline and follow-up, there will be a decrease in the following: a) drug use before sex, b) alcohol use before sex, and c) depressive and/or anxiety symptomatology in intervention branches 3, 4, and 5, compared to branches 1 and 2.

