**Study Instruments and Variables**

Respondents from all study branches will have the opportunity to complete baseline, post-intervention and follow-up assessments, which based upon previous piloting activities, each average about 10 minutes in duration. Survey questions have been adapted from questionnaires used by the research team in their previous online studies and pilot intervention. The online baseline and follow-up questionnaires will include information on the following domains:

- demographics (year of birth, race/ethnicity, education, income and the first 3 digits of the US zip code)

- depression and anxiety symptomatology

- assessment of risk behaviors, such as type of sexual contact (anal, oral, vaginal -- with and without condoms)

- knowledge of partners’ HIV status and disclosure of participants’ HIV status

- drug and alcohol use (in general and use before or during sex)

- how sex partners were met (online versus other ways)

- HIV and STD testing

- knowledge of HIV status

Please see ‘Additional Outcome Variables’ under Primary and Secondary Outcome Variables below. All surveys are located in the Appendices.

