**Primary and Secondary Outcome Variables: Baseline & (60-day) Follow-up Period**

These questions will be included in the baseline survey and the 60-day follow-up surveys

| **Concept** | **Number of Key Variables** | **Primary Outcome Variables** | **Measurement for Statistical Analysis** |
| --- | --- | --- | --- |
| HIV Disclosure: Asked partner(s); partners asked | 4 variables | Likert scale for “asking HIV status” by partner serostatus | (Ordinal), Treated as Continuous |
| HIV Disclosure: Told partner(s); partners told | 4 variables | Likert scale for “telling HIV status” by partner serostatus | (Ordinal), Treated as Continuous |
| HIV testing / Reasons for not getting tested | 10 variables | Number of times tested, last time tested and test result, if HIV negative or unknown will respondent plan to get tested and when? If never tested, reasons for not testing. If HIV-positive, when did they get test result (month/year). | Categorical |
| Current Condom Use | 8 variables | Condom use (receptive and insertive) with new and/or steady partners in past 60 days. | Categorical |

| **Concept** | **Number of Key Variables** | **Secondary Outcome Variables** | **Measurement for Statistical Analysis** |
| --- | --- | --- | --- |
| Drug Use | 15 drugs | Frequency of drug use and typical drugs (route of administration) used in past 60 days. | Continuous, categorical |
| Alcohol Use | 4 variables | Frequency of alcohol use and number of drinks drank (binge drinking) (5+ drinks) before/during sex and in general past 60 days. | Continuous, categorical |
| Depressive Symptoms, last 2 weeks | 2 variables | Positive Depressive Symptom Score: PHQ-2, part of PHQ-4. | Interval (Will be dichotomized) |
| Anxiety Symptoms, last 2 weeks | 2 variables | Positive Generalized Anxiety Disorder Score: GAD-2, part of PHQ-4. | Interval (Will be dichotomized) |
| **Concept** | **Number of Key Variables** | **Additional Variables** | **Measurement for Statistical Analysis** |
| Drug or alcohol treatment | 1 variable | 60-day drug or alcohol treatment (yes, no) | Dichotomous |
| Health seeking behavior | 2 variables | Clicks on treatment links on the survey exit page- do the proportion of clicks vary by intervention branch? | Dichotomous |

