**Multivariate Analysis:** For dichotomous outcomes, we will use logistic regression models to simultaneously examine the effects of predictors found to have a statistically significant association with the binary outcomes in bivariate analyses. Further, logistic regression will allow the introduction of the pretest observation (e.g. asked new partner’s HIV status) and treatment status as predictors and a set of demographic control variables. For continuous outcomes, we will use linear regression models to study quantitative outcome variables such as number of days respondent drank alcohol in the past 60 days (at baseline and 60-day follow-up).

**Analysis of Treatment Branches:** For analysis of within-treatment branches, we will use McNemar’s Test, which is a chi-square test used when data consist of paired observations on a particular outcome (i.e., pre-post treatment design), such as HIV disclosure with a new sex partner. For analysis of between-treatment branches, we will test differences across interventions or group mean differences by employing linear regression with interaction terms. We will also use ANOVA to examine within- and across-branch differences between those who complete the intervention activities and those who do not.

**Safeguarding against Confounding:** To safeguard against confounding in the multivariate logistic regression models, variables not significantly associated with outcomes in simple bivariate analyses may be included for conventional demographic items or if it is highly plausible (either biologically or behaviorally) that they are associated with the outcome.

**Interactions:** Tests for interactions will be conducted between pairs of explanatory factors and binary outcomes to assess possible interactions.

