**ONLINE RESEARCH STUDIES**

***Study 1:* Web-based Survey of Sexual Behavior among Gay and Bisexual Populations**

[name], PI

Between June 3 and July 24, 2002 an anonymous, cross-sectional online survey was conducted, inquiring about general sexual and drug-using behaviors among MSM during a recent 6-month period. The survey was displayed in the chat room area of a gay-oriented website.24, 54, 55 Approximately 6,000 participants clicked on the banner; 2,284 exited the survey without answering any questions; 2,915 men who completed the survey reported sex with other men or self-identified as gay or bisexual. Participants resided in all fifty states. The sample was predominately white (85%). Nearly half of the sample was between 18 and 29 years of age (range 18-60+). Most reported up to $40,000 income and at least some college education or more. Most men (80%) reported having sex only with men. Overall, 8% of the sample reported testing HIV-positive. During the six-month study period 80% reported more than one sex partner. Forty-five percent reported any illicit drug use and about half reported drinking alcohol before or during sex. Approximately 68% of those reporting drug use reported drugs before or during sex. The self-reported HIV prevalence by age group (which included men in the denominator who were not tested during the 6-month period the study asked about) was 2% for 18-24, 6% for 25-29, 12% for 30-39, 10% for 40-49, and 13% for 50 or older.

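### The listed secondary drug outcome is general use over 60 days, while secondary hypothesis (a) concerns drug use before sex; for alcohol, the measure that tests hypothesis (b) is not fixed

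*Protocol*

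**What the plan says.** Under Specific Aims and Hypotheses, Aim 3 lists the outcomes to be compared across the five branches as "HIV disclosure, HIV testing, condom use, drug and/or alcohol use before sex, and depressive and/or anxiety symptomatology". The secondary hypotheses predict a decrease in branches 3 to 5, relative to branches 1 and 2, in "a) drug use before sex, b) alcohol use before sex, and c) depressive and/or anxiety symptomatology".

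The table under Primary and Secondary Outcome Variables gives the secondary drug outcome as "Frequency of drug use and typical drugs (route of administration) used in past 60 days", measured as continuous and categorical. The next row gives the alcohol outcome as "Frequency of alcohol use and number of drinks drank (binge drinking) (5+ drinks) before/during sex and in general past 60 days".

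Study Instruments and Variables says the baseline and follow-up questionnaires cover "drug and alcohol use (in general and use before or during sex".

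In Data Handling and Analysis, the Multivariate Analysis paragraph illustrates linear regression with "number of days respondent drank alcohol in the past 60 days (at baseline and 60-day follow-up". The Bivariate Analysis paragraph mentions change in drug use, again in general terms and again as an example. No sentence there names drug or alcohol use before sex as a dependent variable.

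**The concern.** The videos deal with sexual risk in the setting of alcohol or drug use, and the hypotheses are worded to match. General use over 60 days is a different quantity. It counts use that has nothing to do with sex, so a change in recreational use elsewhere could be read as support for hypothesis (a). It also dilutes, and may partly hide, a change confined to sexual encounters.

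There is a procedural risk as well. An analyst who follows the outcome table tests (a) on the wrong construct; one who follows the hypothesis departs from the listed outcome. For alcohol, two measures are listed and neither is tied to (b). If these choices are left until the data are in, they can be made with the results in view.

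**Working it through.** No design figure needs to be reproduced. The check is whether hypothesis, outcome table, instrument and analysis text name the same behaviour.

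**Drugs**

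| Place in protocol | Behaviour named |
| --- | --- |
| Aim 3 and secondary hypothesis (a) | use before sex |
| Outcome table, drug row | frequency, type and route over 60 days; no mention of sex |
| Study Instruments and Variables | both general use and use before or during sex |
| Appendix F, intention items | intention to cut down drug use before sex |
| Bivariate Analysis example | change in drug use, general |

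Hypothesis, instrument and intention items all refer to the sexual context. The outcome row does not.

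**Alcohol**

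| Place in protocol | Behaviour named |
| --- | --- |
| Aim 3 and secondary hypothesis (b) | use before sex |
| Outcome table, alcohol row | both before/during sex and general |
| Study Instruments and Variables | both |
| Appendix F, intention items | intention to cut down alcohol use before sex |
| Multivariate Analysis example | drinking days, general |

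Here the hypothesised behaviour is among the listed outcomes. What is missing is a statement of which listed measure tests (b), and the only example given is the general one.

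The alcohol row also bears on how to read the drug row. The table separates sex-related from general use for alcohol and gives only general use for drugs, so the drug row cannot simply be assumed to include use before sex.

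**Illustration of how far the two drug measures can differ.** Appendix A, Study 1 (the 2002 survey) reports that 45% of men used any illicit drug in a six-month period, and states: "Approximately 68% of those reporting drug use reported drugs before or during sex".

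- Used before or during sex: 0.45 × 0.68 = 0.306, about 31% of men.
- Used only at other times: 0.45 − 0.306 = 0.144, about 14% of men.
- Share of users without the target behaviour: 0.144 / 0.45 = 0.32, about one third.

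These figures show that the two populations overlap but are not the same. They do not give an effect size for this trial: the window was six months rather than 60 days, the sample was not restricted to men with a recent new partner, and they are prevalences whereas the listed outcome is a frequency.

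**What a frequency measure would register.** Suppose a man stops using drugs on S occasions linked to sex and replaces a fraction r of them with use at other times. His general frequency falls by S × (1 − r). With r = 0 the whole fall appears, with r = 0.5 half of it, and with r = 1 none. The documents give no value for r, so the loss of signal cannot be stated as a single number.

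**The case against.** The strongest reply is that this is one incomplete row label. The table introduces itself as a list of questions to be included in the surveys and gives counts of variables, so it can be read as an inventory rather than as one endpoint per hypothesis. The aim is stated correctly, the data are said to be collected, and choosing the dependent variable from collected items is often left to a statistical analysis plan, which is not at hand.

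Part of this stands. The hypothesis can still be tested from data the protocol says will exist. A reader might infer that the trial as a whole would test a different behaviour, or that hypothesis (a) cannot be tested; neither follows. But the table is headed as the primary and secondary outcome variables and has a column for their measurement in the statistical analysis. The point is therefore a conflict between two protocol statements, not a detail left for later.

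The reply also succeeds on alcohol. The row already includes drinking before or during sex, and the drinking-days regression is introduced only as an example. A reader might infer that hypothesis (b) would be tested on general drinking; the protocol does not say so.

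A further tempting reading is that the measured drug effect would be zero if men dropped drugs before sex but kept using at other times. That requires an any-use measure, or full replacement of the dropped occasions (r = 1). The listed outcome is a frequency and could capture part of the change, so no zero-effect claim is supported.

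Finally, the survey form is a separate document that is not shown, and the protocol gives no recall window for the before/during-sex drug item. The pilot and Study 2 in Appendix A reported drug use in the last encounter. If the present item does the same, an outcome covering the whole follow-up period could not be derived from it. The fix has to allow for that.

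**Conclusion.** The point holds for drugs and, in a narrower form, for alcohol. The secondary drug outcome as listed does not measure the behaviour named in Aim 3 and hypothesis (a). For alcohol, the hypothesised behaviour is listed beside general use, but the measure that tests (b) is not fixed.

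The conclusion on wording rests on the protocol text alone and needs no numerical assumption. Its effect on results cannot be quantified from the documents; the Study 1 shares are background only. The issue is confined to secondary outcomes and has no bearing on sample size, power or the primary comparisons. It is worth correcting because the mismatch is plain and the correction is small.

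**What to change.** 1. In the secondary part of the outcome table, name drug use before or during sex as the outcome for hypothesis (a), in the form in which the survey collects it and over the recall window the survey uses. State that window.
2. In the alcohol row, name the before/during-sex measure as the outcome for hypothesis (b).
3. Keep general drug and alcohol use as additional or supportive measures.
4. In the Multivariate Analysis paragraph, replace or supplement the drinking-days example with the before/during-sex measure, provided its scale suits the model being illustrated.

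The cost is a few words in two table rows and one analysis sentence. Since the protocol says use before or during sex is already asked for both substances, no new question appears to be needed. The survey form should be checked first for the item's wording and recall window.

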**Sampling, Sample Size, and Statistical Power**

The three primary outcomes in this study are increased HIV testing, HIV disclosure, and condom use. Using historical data from the pilot intervention (see Appendix A), we observed that HIV testing increased from 20% to 42% in HIV-negative men between baseline and 3-month follow-up. Based upon these values using a 2-group design (control vs. intervention), with a 5% significance level and 80% power, 77 participants would be required in each study condition for a total sample size of 154. In the current study, which has a 5 branch design, we anticipate that by enrolling 3,000 men and retaining 70% (N=2,111), we will have sufficient power to detect meaningful differences in behavior among the study branches.

Although we will be comparing within and across all study branches, we expect the greatest differences to be found between control branch 1 and branch 5 (both videos) for the primary outcomes. The Bonferroni correction will be used to protect the overall Type I error rate with multiple comparisons. In these comparisons, the nominal significance level will be set to alpha = 0.05 for two-sided tests (divided by the number of pairwise comparisons for individual tests). Using Chi-square tests to detect behavioral changes between the binomial primary outcomes, we obtain the following powers to detect a difference between two study branches for various true proportions and sample sizes (α=0.05; 10 pairwise comparisons).

| **Power Calculations for Meaningful Differences**  **between Study Branches** | | | | | |
| --- | --- | --- | --- | --- | --- |
| **Behavior Change Outcomes†** | | **Sample Size per Branch* and Associated Power** | | | |
| Branch A | Branch B | N = 300 | N = 400 | N = 500 | N = 600 |
| 0.10 | 0.15 | 0.142 | 0.221 | 0.308 | 0.396 |
| 0.10 | 0.20 | 0.709 | 0.865 | 0.944 | 0.979 |
| 0.10 | 0.25 | 0.978 | 0.997 | >.999 | >.999 |
| 0.15 | 0.20 | 0.097 | 0.150 | 0.210 | 0.275 |
| 0.15 | 0.25 | 0.569 | 0.747 | 0.863 | 0.931 |
| 0.15 | 0.30 | 0.939 | 0.988 | 0.998 | >.999 |
| 0.20 | 0.30 | 0.476 | 0.652 | 0.784 | 0.874 |
| 0.20 | 0.35 | 0.894 | 0.971 | 0.993 | 0.999 |
| 0.20 | 0.40 | 0.994 | >.999 | >.999 | >.999 |
| 0.30 | 0.40 | 0.375 | 0.536 | 0.673 | 0.780 |
| 0.30 | 0.45 | 0.821 | 0.936 | 0.980 | 0.994 |
| 0.30 | 0.50 | 0.984 | 0.998 | >.999 | >.999 |
| 0.40 | 0.50 | 0.336 | 0.488 | 0.623 | 0.733 |

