**Standardized Measures Included in Instruments**

Depression and Anxiety Symptoms: The Patient Health Questionnaire for Depression and Anxiety (PHQ-4)51 is a four-item scale that will be used. The PHQ-4 comprises the PHQ-2, which assesses depressed mood and anhedonia, and the GAD-2, which assesses generalized anxiety disorder. The PHQ-4 begins with the stem question: “Over the last 2 weeks, how often have you been bothered by the following problems?” The four screening questions are: Feeling nervous, anxious, or on edge; Not being able to stop or control worrying; Feeling down, depressed, or hopeless; and Little interest or pleasure in doing things. Responses are scored as 0 (“not at all’), 1 (“several days”), 2 (“more than half the days”), or 3 (“nearly every day”). The total score on this composite measure ranges from 0 to 12 (the score range for both the PHQ-2 and GAD-2 is 0 to 6). Kroenke and colleagues measure depression and anxiety screens separately. Thus, if a participant scores 3 or higher on either the PHQ-2 or the GAD-2, then he will have screened positive for that mental health problem. A score of 3 is considered the optimal cut-point for screening purposes.52, 53

Reasons for Not Getting Tested: We will be using a slightly adapted version of the CDC sponsored HIV testing Survey (HITS), which inquires about the various reasons people don’t get tested. The instrument targets HIV-negative or untested individuals at-risk for HIV infection.

Defining Sex Partners:The definition of male or female main partner for this study is: Main Partner (boyfriend [or girlfriend], spouse, significant other, or life partner). This definition will be used for the 60 days prior to and after baseline. We will be able to determine new partners (first sex within the past 60 days) from the question, “When did you first have sex with xxx?” The response options are (‘within the last’) 24 hours, 7 days, 30 days, 60 days, 1 year, more than a year ago. If the respondent chooses 60 days or sooner, then we know this was a new partner.

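### Cutting the PHQ-2 and GAD-2 scores at a screening threshold loses much of the power to detect the hypothesised decrease in symptoms

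*Protocol*

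**What the plan says.** Under Specific Aims and Hypotheses, the Aim 3 secondary hypotheses predict a decrease from baseline to follow-up in "depressive and/or anxiety symptomatology in intervention branches 3, 4, and 5, compared to branches 1 and 2".

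Standardized Measures Included in Instruments describes the two scales. It notes that "the score range for both the PHQ-2 and GAD-2 is 0 to 6" and that "if a participant scores 3 or higher on either the PHQ-2 or the GAD-2, then he will have screened positive". It gives the purpose of that threshold: "A score of 3 is considered the optimal cut-point for screening purposes".

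The table under Primary and Secondary Outcome Variables has a column for the form in which each variable will be analysed. The depression outcome is named "Positive Depressive Symptom Score: PHQ-2, part of PHQ-4", with a matching row for the GAD-2, and the entry in both rows is "Interval (Will be dichotomized". In the same table the ordinal Likert items on asking and telling HIV status are to be treated as continuous.

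The Multivariate Analysis paragraph assigns logistic regression to dichotomous outcomes and linear regression to continuous ones, so the entry in the table also settles the model. The protocol states no score-based analysis of these two scales and no power for them.

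**The concern.** The hypothesis concerns the level of symptoms, while the planned outcome records only which side of a case-finding threshold a man is on. A fall from 6 to 3 leaves him positive and a fall from 2 to 0 leaves him negative, although both are decreases in symptoms. A man below 3 at baseline cannot register any improvement.

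A real branch effect on symptoms is therefore more likely to be missed, and a non-significant result would say less about symptoms than the collected data could support. The protocol itself commits to the dichotomisation, so this is not a detail left to a later analysis plan.

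**Working it through.** **1. Inputs from the protocol.**
- Scores run from 0 to 6, with a cut at 3 (Standardized Measures).
- 600 men are planned per branch. Expected attrition is 240 in each of branches 1 and 2 and 180 in each of branches 3 to 5 (Attrition and Retention Efforts). This leaves 600 − 240 = 360 and 600 − 180 = 420.
- In the power section "the nominal significance level will be set to alpha = 0.05 for two-sided tests", divided over 10 pairwise comparisons: 0.05/10 = 0.005. That text is written for the primary outcomes, so both 0.05 and 0.005 are shown below.

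**2. The protocol's own power figures.** They cover the primary outcomes only. The two-proportion normal approximation with continuity correction at two-sided 0.005 gives, for 0.20 against 0.30, 0.471, 0.648, 0.781 and 0.872 at N = 300, 400, 500 and 600. The table prints 0.476, 0.652, 0.784 and 0.874. Every numeric cell is reproduced within 0.013. The stated 77 per group for 20% against 42% compares with 78 with continuity correction and 69 without.

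**3. Loss from cutting, by formula.** For a normal score cut so that a share p lies at or above c, the cut keeps φ(c)²/[p(1 − p)] of the information (RE). If the full score has 80% power, the cut has power Φ[(z₁₋α/₂ + 0.842)·√RE − z₁₋α/₂]. The protocol does not give p, so a range is assumed. For p = 0.20, c = 0.842 and φ(c) = 0.280, so RE = 0.0784/0.16 = 0.49. Power at 0.05 is then Φ(2.802 × 0.70 − 1.960) = 0.50.

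| Share at 3 or more (assumed) | Information kept | 360 men worth | Power at 0.05 (score: 80%) | Power at 0.005 (score: 80%) |
| --- | --- | --- | --- | --- |
| 50% | 0.64 | 229 | 61% | 54% |
| 40% | 0.62 | 224 | 60% | 53% |
| 30% | 0.58 | 207 | 57% | 49% |
| 20% | 0.49 | 176 | 50% | 40% |
| 10% | 0.34 | 123 | 37% | 25% |

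**4. Loss on a discrete 0 to 6 score, 360 against 420 men.** Two items scored 0 to 3 are generated from correlated latent normals, one branch is shifted uniformly, and a test of means is compared with a test of proportions at 3 or more. There is no baseline adjustment.

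*Setting A* (latent correlation 0.65, shift 0.22 SD, 4,000 simulated trials per setting, two-sided 0.05):

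| Share at 3 or more | Power, score | Power, cut |
| --- | --- | --- |
| 10% | 0.77 | 0.45 |
| 15% | 0.82 | 0.57 |
| 25% | 0.85 | 0.65 |

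*Setting B* (latent correlation 0.6, different item thresholds, shift 0.2 SD):

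| Share at 3 or more | Score v cut, 0.05 | Score v cut, 0.005 | Information kept |
| --- | --- | --- | --- |
| 10% | 0.700 v 0.395 | 0.374 v 0.135 | 0.45 |
| 20% | 0.775 v 0.546 | 0.464 v 0.234 | 0.58 |
| 30% | 0.808 v 0.630 | 0.510 v 0.304 | 0.65 |
| 40% | 0.827 v 0.671 | 0.537 v 0.343 | 0.69 |

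With a shift of 0.3 SD in Setting B at 0.005, the figures are 0.80 v 0.37, 0.89 v 0.59, 0.92 v 0.72 and 0.94 v 0.78.

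**5. Does the loss depend on the contrast or the effect size?** If the hypothesis is read as a pooled contrast, the groups are 2 × 360 = 720 and 3 × 420 = 1,260. A further run varied the shift from 0.10 to 0.22, the contrast (pairwise or pooled) and the significance level (0.05 or 0.005). The cut kept about 46% to 64% of the information throughout.

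**The case against.** The planned quantity is declared and familiar: the outcomes are named as positive screens, and a fall in the share screening positive is one legitimate reading of a decrease in symptomatology. On that view, moving to a mean difference changes the estimand and does not correct an error. It is true that nothing in the protocol is misstated. But the protocol gives no reason for the cut beyond screening, and the same table treats coarser Likert items as continuous.

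The absolute power figures also depend on choices the protocol does not supply.
- *Pooled contrast.* With 720 against 1,260 men and a 0.22 shift, power is about 0.98, 0.99 and 0.99 with the score, and 0.78, 0.87 and 0.95 with the cut, at 10%, 15% and 25% positive. The gap is smaller there, but at a shift of 0.15 it is again 0.80 to 0.88 against 0.50 to 0.71.
- *Pairwise at 0.005.* For a shift near 0.2, both analyses are underpowered, so scoring alone would not rescue that comparison.
- *A smaller effect.* The videos are short and are not described as addressing depression or anxiety. At a shift of 0.10, pairwise power at 0.05 is about 0.24 to 0.28 with the score and 0.14 to 0.20 with the cut: low either way.

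These points stand as limits on absolute power. They do not remove the relative loss.

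The score also has a floor: in models of this kind about 38% to 61% of men score 0 and cannot improve. That is a real limitation of the score, but the simulations in step 4 already use bounded 0 to 6 scores, and under the cut every man below 3 is in the same position. Finally, a non-significant result never proves no effect, whichever analysis is used; the score analysis simply leaves less uncertainty about symptoms.

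**Conclusion.** The concern holds. The protocol fixes a dichotomised analysis for a hypothesis about a decrease in symptoms, using a threshold that it describes as one for screening.

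Over the assumed range of screen-positive shares, the cut keeps 34% to 64% of the information by the normal-score formula and about 44% to 69% on simulated 0 to 6 scores. A comparison with 80% power on the score falls to 37% to 61% at 0.05 by the formula. The loss is greatest when few men screen positive.

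The exact size cannot be computed, because the protocol gives no distribution, screen-positive share or effect size for these scales. The figures assume a shift across the whole score. The loss would be smaller if the effect lay mainly near the cut or if the score analysis already had power close to 100%; the protocol gives no reason to expect either. The outcomes are secondary and the primary comparisons are untouched, so this is a worthwhile improvement rather than a threat to the trial.

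**What to change.** In the PHQ-2 and GAD-2 rows of the outcome table, replace the dichotomised entry with the 0 to 6 score. State that each score at 60 days will be analysed by linear regression on branch, adjusted for the baseline score; ordinal regression is a reasonable alternative given the floor at 0. Keep the share scoring 3 or more, by branch and time point, as a descriptive supplement.

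The cost is wording only: the scores are already collected and linear regression is already in the plan. Baseline adjustment should add precision beyond the unadjusted figures above. The drawbacks are that a mean difference on a two-item scale is less familiar than the percentage screening positive, which would still be reported, and that men scoring 0 still cannot improve.
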